### Limitations

Placebos for procedures like *Vamana* and *Virechana* are challenging to include; therefore, this study does not include a control group. However, the resulting single-group study design raises concerns about internal validity.

In addition, this exploratory pilot trial lacks a concurrent, untreated parallel control group. Since this study operates as an investigator-initiated doctoral project embedded within a real-world clinical service, introducing an untreated healthy cohort was operationally and ethically unfeasible, as all recruited individuals are actively seeking immediate wellness interventions. To mitigate this constraint and maximize data validity, each participant serves as their own internal longitudinal control through structured pre- and postintervention paired comparisons. Furthermore, potential lifestyle and environmental confounding variables are strictly controlled by housing all 53 participants within an identical inpatient ward environment throughout the active study timeline.

We acknowledge that serum MDA and T-SOD are short-term surrogate markers of oxidative stress, not direct proof of delayed aging. In this protocol, *Śodhana* represents a complete therapeutic process including *Pūrvakarma* (internal oleation), *Pradhāna Karma* (*Vamana* or *Virechana*), and *Saṃsarjana Krama*. Therefore, acute changes in MDA and T-SOD reflect the immediate metabolic shifts of this entire multiphase cycle rather than long-term aging changes. To address this limitation, we paired these dynamic redox markers with telomerase activity. This allows us to explore whether the intense physiological “reset” caused by the complete *Śodhana* sequence correlates with any stabilizing effects on a deeper, genetic marker of cellular longevity.

The sample size calculation was also pragmatic rather than inferential. The exploratory nature of the study warrants a focus on feasibility of the protocol rather than to test the hypothesis.

The recruitment is seasonal and consecutive. Therefore, differences in environmental factors, including the climate and diet, as well as baseline biological rhythms between the 2 cohorts may act as potential modifiers for biomarker levels.

Although other biomarkers, including an interleukin panel and the microbiome, are available, we included only a limited number of biomarkers for our healthy volunteers due to financial constraints.

Regardless of these limitations, the study will generate preliminary evidence of how these procedures can affect oxidative stress levels. This could facilitate introducing *Vamana* and *Virechana* as preventive procedures in additional medical arenas other than as a preventive aging intervention. The data regarding change in the telomerase activity and telomere length will provide a new avenue for further studies.

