**Methods:**

The study was prospectively registered in the Clinical Trial Registry-India (CTRI; CTRI/2024/02/062176), uses a pre-posttest study design, and includes 53 participants 35 years to 65 years old. The study is exploratory and lacks a control group. Those with a BMI between 18.5 kg/m^2^ and 25 kg/m^2^, with stable weight for 3 months immediately prior to the study, with *madhyama koshta* (medium nature of bowel evacuation, as assessed using aquestionnaire), who are *Vamanarha* (eligible for therapeutic emesis) and *Virechanarha* (eligible for therapeutic purgation), and who do not meet the exclusion criteria will be included in the study. The interventions include emesis in the spring and purgation in the autumn season, preceded by *Snehana* (oleation) and *Swedana* (fomentation) and followed by the *Samsarjana karma* (specialized menu of diets) depending on the measurement of purification. Trial duration will range from 18 days to 20 days for each participant, and the total study duration will be 3 years. The serum levels of MDA, SOD, and telomerase activity will be measured on day 0 and on the next day following completion of the *Samsarjana karma* (18th-20th day). Continuous variables for primary biological endpoints including serum MDA, T-SOD, and telomerase activity will be evaluated using paired-samples *t* tests or Wilcoxon signed-rank tests, with potential missing data managed under a missing completely at random assumption using available case analysis (pairwise deletion) cross-verified by a conservative baseline observation carried forward (BOCF) sensitivity test. The effect size will be also determined.

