### Study Objectives

#### Primary Objective

The primary objective is to evaluate *Vamana* in *Vasanta ritu* (spring season) and *Virechana* in *Sharad ritu* (autumn season) for modulating systemic oxidative stress by measuring the reduction in serum levels of MDA and enhancement of SOD activity from baseline to postintervention.

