## Methods

### Trial Design

This open-label, exploratory clinical trial consists of a single group and a primary endpoint of decreasing serum MDA values and increasing serum SOD values within 18 days to 20 days after *Vamana* in *Vasantha ritu* and *Virechana* in *Sarad ritu*. The participants will be recruited by the principal investigator consecutively by season: *Vamana* cohort in the *Vasantha ritu* (spring season) and *Virechana* cohort in the *Sarad ritu* (autumn season). Each participant is enrolled into only one seasonal arm based strictly on their chronological window of voluntary registration. There is no active assignment of participants; instead allocation follows a participant-driven, self-selection framework. The total study duration is 3 years. The study is registered in the Clinical Trial Registry-India (CTRI; CTRI/2024/02/062176).

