#### *Pradhana Karma* (Main Procedure)

*Virechana* will be completed using *Trivrit Lehya* (drug prepared from *Operculina turperthum*) at around 7 AM.

For *paschat karma* (the postoperative procedure), after attaining hunger and when the participant ceases to feel the urge for defecation, he/she will be allowed to take a bath in warm water.

Based on the *sudhi lakshana* (signs and symptoms suggestive of a proper purgation), the participant will be advised to follow *samsarjana* (modified dietic regimen) for 1, 2, or 3 days.

The participants will be admitted to the hospital for the duration of the trial. The administered diet will be uniform for all participants. Hydration will also be monitored. Participants are restrained from doing strenuous physical activity throughout the intervention. They are also advised to sleep for a strict 6 hours to 8 hours. The strictly enforced controls on diet, hydration, physical exertion, and sleep are not external protocol restrictions but standardized, fundamental therapeutic components (*Ahara* and *Vihara*) inherent to the classical *Śodhana* (Panchakarma) and *Samsarjana Krama* (graduated postdetox dietary timeline) intervention package. These parameters are operationally deployed within an institutional setting to ensure uniform clinical delivery.

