### Future Directions

As an exploratory and hypothesis-generating pilot study, the definitive dataset generated from these 53 participants will establish the baseline standard deviations and accurate effect sizes required to design future research. The immediate next phase of this work will involve developing a fully powered, multi-arm, randomized controlled trial. This future trial will introduce a parallel, nontreatment control group or a fasting-mimicking dietary control arm, which is necessary to cleanly separate the unique cellular detoxification effects of active *Śodhana* from simple caloric restriction.

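### Identical ward housing does not control lifestyle confounding of a single-group pre-post change, because the ward regimen is itself part of what changes between the two samples

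*Protocol article*

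**What the plan says.** **Design and contrast.** The Trial Design section states: "This open-label, exploratory clinical trial consists of a single group". Under Trial Estimand, the comparison is each participant's pre-intervention state (T0) against the state after the inpatient package (T1), summarised as the mean within-person change over the pooled 53. The abstract adds that the markers "will be measured on day 0 and on the next day following completion of the" graduated diet, on day 18 to 20.

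**The mitigation claim.** The Limitations section concedes that there is no control group and that this raises a question of internal validity. It then offers two mitigations. The first is that "each participant serves as their own internal longitudinal control through structured pre- and postintervention paired comparisons". The second is that "potential lifestyle and environmental confounding variables are strictly controlled by housing all 53 participants within an identical inpatient ward environment".

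**The role of the ward regimen.** The Virechana section on the main procedure says participants are admitted for the trial's duration, eat a uniform diet, have hydration monitored, avoid strenuous activity and sleep 6 to 8 hours. It then says: "The strictly enforced controls on diet, hydration, physical exertion, and sleep are not external protocol restrictions but standardized, fundamental therapeutic components".

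**How the result is to be read.** The Primary Objective is to evaluate Vamana and Virechana "for modulating systemic oxidative stress by measuring the reduction in serum levels of MDA and enhancement of SOD activity from baseline to postintervention". The close of the Limitations discussion expects preliminary evidence on what the procedures do to oxidative stress. Future Directions proposes a control arm in a later trial, "which is necessary to cleanly separate the unique cellular detoxification effects of active" Śodhana from caloric restriction.

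**The concern.** The protocol gives the same ward regimen two roles that do not fit together. In the intervention section it is a component of the treatment. In the Limitations section it is the means by which confounding is controlled. A component that starts with the treatment in every participant cannot also serve as the control for it.

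What is at stake is attribution. A significant fall in MDA or rise in SOD could be reported as an effect of emesis or purgation with lifestyle factors ruled out. The design supports only a narrower statement: the markers changed over a stay in which diet, rest, sleep, oleation, the main procedure and the graduated diet all changed together.

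**Working it through.** **1. What the contrast contains.** For participant *i*, the change T1 − T0 can be written as

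change_i = (procedure effect) + (ward-regimen effect) + (anything else that shifts with time) + individual deviation.

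The paired test asks whether the mean of change_i is zero. A regimen effect common to all 53 participants goes wholly into that mean. Uniform housing can reduce the spread of the individual deviations. It leaves the common shift in place and, by reducing the spread, can make that shift easier to detect.

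**2. Whether the planned analyses can remove it.**
- Pairing removes stable differences between people, not changes that occur in everyone.
- The regression under Statistical Measures adjusts for baseline value, age, sex and BMI. Ward exposure is the same for every participant, so it has no variation to adjust on.
- The Vamana-versus-Virechana comparison does not help, because both cohorts are inpatients under the regimen.

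**3. Timing.** T0 is defined as pre-intervention, and the regimen is defined as part of the intervention. It follows that the regimen is in force at T1 and not at T0. The order of admission and the day-0 draw is not stated outright, so this is an inference. The Exclusion Criteria mention a preconditioning period on study food, but no run-in before the day-0 sample is described.

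**4. The protocol's own figures.** From the Sample Size section: Z = 1.96, P = .5, d = 0.15, dropout 20%.
- 1.96² × 0.5 × 0.5 / 0.15² = 42.68, and 42.68 / 0.80 = 53.35, consistent with the stated 53.
- A two-sided paired *t* test with n = 53, Cohen d = 0.395 and α = .05 has noncentral-*t* power 80.6%, consistent with the stated 80%.

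Both figures reproduce, and the present point does not depend on them.

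**5. Illustration of size.** Assume that the procedures have no effect and that the regimen alone shifts a marker by *s* SD of the change score in the favourable direction. The values of *s* are assumptions; the protocol gives none.

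- Smallest mean change giving P<.05: t(0.975, 52)/√53 = 2.007/7.280 = 0.276 SD.
- Joint criterion: the Primary Outcome section asks for P<.05 together with a moderate to large Cohen d, and Statistical Measures puts medium at 0.5. If that is read as an observed d of at least 0.5, the *t* statistic must reach 0.5 × √53 = 3.640. This also guarantees P<.05.
- Noncentrality: s × √53, with 52 degrees of freedom.

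| Assumed shift *s* | Noncentrality | Chance of P<.05 | Chance of P<.05 and observed d ≥ 0.5 |
|---|---|---|---|
| 0.2 | 1.456 | 30% | 2% |
| 0.3 | 2.184 | 57% | 9% |
| 0.395 | 2.876 | 81% | 24% |

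These are ordinary power values. They show how readily the test would respond to a shift of that size, not that such a shift exists.

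**The case against.** **The package is already the estimand.** The estimand names an inpatient package, the intervention section calls the regimen a therapeutic component, and the Limitations section says that changes in MDA and T-SOD reflect the full multi-phase cycle. For a package effect the regimen is a component, not a confounder. This stands, and it is why the fault is confined to wording that departs from that definition. It does not rescue the sentence about ward housing, which claims a control that a package reading neither needs nor has.

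**The missing control is disclosed.** The abstract, Limitations and Future Directions all say so, and the abstract's conclusion claims only hypothesis-generating evidence. This stands too. A reader might infer that the trial hides its main weakness or has committed itself to a causal conclusion; the text does not support that. The trouble is that the mitigation sentence takes back part of the admission.

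**The direction is unknown.** A reader might infer that rest, supplied food and sleep would produce the hoped-for result on their own. The protocol does not establish this. Its Discussion cites a 21-day fast as influencing MDA, but also cites high-intensity running as lowering MDA and raising SOD, while the ward bars strenuous activity. Participants must also give up antioxidants and supplements. No section describes the ward diet as a sustained fast. Some of the concurrent changes could therefore work against the hypothesis.

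**P<.05 alone is not the criterion.** Correct: the Primary Outcome section also asks for a moderate to large effect size, which is why the table carries the last column.

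**Different diets or seasons.** A reader might also see a contradiction between an identical ward and the admitted differences in climate and diet between the cohorts, or the pre-procedure diet given only for Vamana. This is weak. Season can differ around the same ward, diet there may mean background diet, and the Vamana diet is a specified intervention step.

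**Conclusion.** The claim that ward housing strictly controls lifestyle and environmental confounding is wrong for a single-group pre-post contrast. Housing standardises conditions between participants. The regimen still changes together with the intervention, and its contribution cannot be separated from that of emesis or purgation by any analysis described. The Primary Objective and the closing Discussion wording credit the procedures, which does not match the package effect that the estimand defines.

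The conclusion rests on the regimen starting after the T0 sample, which follows from the protocol's definitions but is not stated directly. The percentages rest on assumed shifts, an assumed favourable direction and, for the joint criterion, reading moderate as an observed d of at least 0.5. The logical point needs none of these numbers.

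Severity is moderate. Much of the correct framing is already in the document, and no endpoint, sample size or analysis is invalidated. What changes is what a positive result may be said to show.

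**What to change.** - **Limitations:** replace the sentence on ward housing. Say that housing standardises conditions between participants, but that supplied diet, hydration, restricted exertion and sleep change together with the intervention, so housing does not control confounding of the pre-post change.
- **Primary Objective and the close of the Limitations discussion:** align both with the estimand, so that a significant change is read as the change over the whole inpatient Śodhana package and is not attributed to Vamana or Virechana alone.
- **Primary Outcome:** adjust the interpretive wording lightly in the same sense.
- **Trial Design or Outcome Measures:** state whether the day-0 sample is drawn before or after admission and the start of study food, so that the timing need not be inferred.

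The cost is wording only, with no new data, participants or analyses. The protocol reports that data analysis is pending, so the interpretation can be settled before results are known. The price is a narrower conclusion.

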### Future Directions

As an exploratory and hypothesis-generating pilot study, the definitive dataset generated from these 53 participants will establish the baseline standard deviations and accurate effect sizes required to design future research. The immediate next phase of this work will involve developing a fully powered, multi-arm, randomized controlled trial. This future trial will introduce a parallel, nontreatment control group or a fasting-mimicking dietary control arm, which is necessary to cleanly separate the unique cellular detoxification effects of active *Śodhana* from simple caloric restriction.
